# Home-based virtual reality training after discharge from hospital-based stroke rehabilitation: a parallel randomized feasibility trial

**DOI:** 10.1186/s13063-019-3438-9

**Published:** 2019-06-07

**Keywords:** Virtual reality, Stroke, Telerehabilitation, Rehabilitation, Technology

## Abstract

**Background:**

Virtual reality training (VRT) uses computer software to track a user’s movements and allow him or her to interact with a game presented on a television screen. VRT is increasingly being used for the rehabilitation of arm function, balance and walking after stroke. Patients often require ongoing therapy post discharge from inpatient rehabilitation. Outpatient therapy may be limited or inaccessible due to waiting lists, transportation issues, distance etc.; therefore, home-based VRT could provide the required therapy in a more convenient and accessible setting. The objectives of this parallel randomized feasibility trial are to determine (1) the feasibility of using VRT in the home post stroke and (2) the feasibility of a battery of quantitative and qualitative outcome measures of stroke recovery.

**Methods:**

Forty patients who can stand for at least 2 min and are soon to be discharged from inpatient or outpatient rehabilitation post stroke are being recruited in Ottawa, Canada and being randomized to control and experimental groups. Participants in the experimental group use home-based VRT to do rehabilitative exercises for standing balance, stepping, reaching, strengthening and gentle aerobic fitness. Control group participants use an iPad with apps selected to rehabilitate cognition, hand fine motor skills and visual tracking/scanning. Both groups are instructed to perform 30 min of exercise 5 days a week for 6 weeks. VRT intensity and difficulty are monitored and adjusted remotely. Weekly telephone contact is made with all participants. Ability to recruit participants, ability to handle the technology and learn the activities, compliance, safety, enjoyment, perceived efficacy and cost of program delivery will be assessed. A battery of assessments of standing balance, gait and community integration will be assessed for feasibility of completion within this population and potential for improvement following the intervention. Effect sizes will be calculated.

**Discussion:**

The results of this study will be used to support the creation of a definitive randomized controlled trial on the efficacy of home-based VRT for rehabilitation post stroke.

**Trial Registration:**

ClinicalTrials.gov, NCT03261713. Registered on 21 August 2017. Registration amended on 1 June 2018 to decrease enrollment from 40 to 20 due to a cut in study funding and difficulty recruiting participants.

**Electronic supplementary material:**

The online version of this article (10.1186/s13063-019-3438-9) contains supplementary material, which is available to authorized users.

## Introduction and objectives

Stroke causes approximately 17,600 hospital admissions per year in Ontario and 50% of individuals who have had a stroke are left with moderate to severe impairment [1, 2]. Most patients who are discharged from inpatient stroke rehabilitation are only 8–10 weeks post stroke and have not completely recovered. Their central nervous systems are still in a period of enhanced neuroplasticity, during which great functional change can be made [3, 4]. Therapy outcomes are dose-dependent; intensive, high-repetition, task-oriented and task-specific therapies are most effective [5, 6]. Therefore, for the greatest recovery possible, these patients require ongoing, intensive therapy. Most are offered this on an outpatient basis. However, for many reasons (transportation difficulties, distance from the rehabilitation center, weather etc.), not all eligible patients are able to attend outpatient therapy. Also, there is a waiting list and a limited number of outpatient therapy sessions are offered to each patient. Home-based therapy may fill an important role towards increasing the availability of rehabilitation, enabling patients to enhance or prolong their therapy and potentially improving outcomes.

Non-immersive virtual reality training (VRT) uses computer software to track the user’s movements and allow him or her to interact with a game or activity presented on a TV screen. It is convenient, timely, enjoyable and may be used for an unlimited period post stroke [7, 8]. VRT has been shown to benefit upper extremity function, standing balance, gait and overall function in the sub-acute and chronic phases post stroke, at least as much as or more than conventional therapy [7, 9–13].

Home-based VRT offers a promising addition or alternative to existing rehabilitation programs that could make a significant difference in the lives of stroke survivors. A few preliminary studies have investigated the use of home-based VRT for standing balance and upper extremity recovery after stroke and shown potential feasibility of these systems for ongoing rehabilitation in the home [14–18]. Some VRT platforms allow the user to interface via tactile devices (for example, a dynamic standing frame [14] or robotic glove [18]) while others use motion-tracking via a camera [16]. Some platforms use asynchronous monitoring to allow the therapist to monitor VRT usage and performance after the actual event [16] while others use synchronous monitoring to enable the therapist to watch in while the participant exercises; some even require constant real-time patient/therapist interaction [17, 19] throughout the therapy session. Users report high satisfaction with home-based VRT [16, 17], although actual usage can vary greatly [18]. Barriers to the use of home-based VRT include technical issues and lack of previous technical experience [18]. While some previous experience with computers is helpful, those who play video games regularly can become bored with VRT. Facilitators include the flexibility of home-based exercise, support from family and motivation from the VRT itself. Early results, available from a single randomized controlled trial (RCT) with 30 participants, suggest that home-based VRT improves standing balance and gait equally to in-clinic VRT, but that the costs are 44% lower [16].

We wish to add to these early studies of home-based VRT using a virtual reality system (Jintronix Inc.) that was initially developed for stroke rehabilitation and has also been used extensively with healthy and frail elderly individuals. The Jintronix system is marketed for institutional and home use and has a simple-to-use interface, but its home use has not yet been fully evaluated. The games are designed to incorporate motor learning principles such as multiple forms of feedback and task-specific practice that can be progressed to maintain an appropriate level of challenge. Unlike systems used in previous research, the Jintronix system includes a wide selection of games and exercises designed for the rehabilitation of sitting and standing balance, gait and upper extremity use. The system is simple to use and relatively inexpensive; a motion-tracking camera and software eliminates the need for gloves/controllers etc. It is straightforward enough for the patient to use independently; asynchronous monitoring is used to track usage and the therapist can change games and parameters remotely. The purpose of this study is to investigate the feasibility, acceptance and safety of this new, simple-to-use VRT system for use in the home, combined with asynchronous, remote support for the user. The results of this trial will support a definitive RCT in the future.

The primary objective is to assess the feasibility of using VRT in the home with patients post stroke, using quantitative and qualitative methods. Specific objectives are:To estimate the recruitment rate of participants into the study;To assess the ability and compliance of the participants with respect to the components of the research protocol (ability to learn VRT through the training program; ability to comply with the exercise protocol; participant retention);To determine the safety of home-based VRT (presence of minor and major adverse events);To assess the ability of stroke survivors and their study partners to use VRT technology in the home (i.e. technical difficulties, difficulty learning the games);To assess the acceptability of the VRT intervention (enjoyment; perceived efficacy);To estimate the cost for a future definitive RCT on in-home VRT.

The secondary objective is to assess the feasibility of the outcome measures, using quantitative and qualitative methods. Specific objectives are:To assess the feasibility and acceptance of a battery of outcome measures, including physical assessments, questionnaires, an interview and a log book;To assess the potential that home-based VRT might maintain or improve physical outcomes of standing balance, gait and general function and community integration after discharge from hospital-based stroke rehabilitation, compared to those who perform a program of iPad apps designed for fine hand motor skills and cognitive training;To determine the sample size required for a future definitive RCT on in-home VRT.

This study is a prospective, single-site, single-blinded, parallel-group (1:1 ratio) randomized, superiority feasibility trial on the use of VRT for ongoing stroke rehabilitation after discharge from inpatient or outpatient stroke rehabilitation. A feasibility RCT was chosen in order to provide the most useful results to prepare for a future definitive RCT on the efficacy of home-based VRT. iPad apps were chosen as a comparator to VRT because they provide a control group that has equal contact with the researchers and equal time spent in an engaging activity. The use of an active control group (rather than providing control group participants with nothing) was also chosen to facilitate recruitment. The iPad apps chosen to work on hand fine motor control and cognition were not deemed to have any influence on the physical outcome measures of standing balance, gait and gross motor function. The Standard Protocol Items: Recommendation for Interventional Trials (SPIRIT) checklist is available as Additional file 1: Figure S1.

## Methods

### Ethics, consent and permissions

This research is being performed in accordance with the Declaration of Helsinki. Approval was obtained from the Élisabeth Bruyère Research Institute (M16-17-013) and University of Ottawa (A01-15-03) (Canada) Research Ethics Boards. Potential participants are informed of study details, including procedures, risks and benefits, confidentiality and the voluntary nature of participation, before signing the consent form.

### Participants

Potential participants have been recruited from the inpatient and outpatient stroke rehabilitation programs at Élisabeth Bruyère Hospital in Ottawa, ON, Canada, since May 2017. Élisabeth Bruyère Hospital is the largest provider of rehabilitation services for stroke in the Champlain Local Health Integration Network in Eastern Ontario and admits approximately 250 stroke survivors to its inpatient program and 250–300 to its outpatient program each year.

Stroke survivors are eligible for the trial if they (1) have had a stroke (ischemic or hemorrhagic) resulting in physical impairment; (2) have sufficient preserved cognitive ability to learn VRT; (3) are receiving inpatient or outpatient stroke rehabilitation services; (4) are able to stand independently for at least 2 min; (5) have a study partner who can attend two training sessions with the participant and is able to be in the home when the participant is doing VRT; (6) can read, speak and understand English; (7) live within 50 km of Élisabeth Bruyère Hospital; (8) are able and willing to attend four appointments at Élisabeth Bruyère Hospital (two for assessment, two for training); (9) will not be travelling away from home for more than 2 days a week for the duration of the study and (10) have sufficient space in their home to do VRT safely. Patients are excluded if they have an unstable medical condition, seizures or vertigo, or are unable to safely perform mild to moderate exercise. Participation in other, non-VRT exercise or rehabilitation programs post discharge does not influence their eligibility in this feasibility trial. The presence of expressive aphasia is not a definitive exclusion criterion.

Members of a patient’s circle of care (physicians, residents, nurses, physiotherapists, occupational therapists, outpatient program triage nurse and social workers or their students) screen patients for the study using the aforementioned criteria. If the criteria are met, the member of the patient’s circle of care asks the patient if he or she would like to hear about a study using video games and exercise at home. If the patient consents verbally, their name is identified to the research associate (RA), who approaches the patient and provides full details on the study. Interested patients are given an opportunity to ask questions before written informed consent is obtained.

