### Randomization, allocation and blinding

Participants are enrolled by the RA. A computer-based randomization system (Sealed Envelope, London, UK) is used to allocate participants in a 1:1 ratio to either experimental or control groups, using permuted blocks while maintaining concealment. The research physiotherapist (PT) accesses the system immediately after the participant is enrolled; the allocation is provided immediately. The only person blinded to treatment allocation is the RA, who performs the outcome measures. The research PT is blinded to the results of the outcome measures. If the participant is undergoing rehabilitation during the study period (for example, outpatient or community-based rehabilitation), the rehabilitation professional is informed of their patient’s participation in the study, to ensure that the home-based exercise is compatible with the participant’s therapy. The PT will reveal a participant’s allocation in the case of serious adverse effects.

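### Patients leaving inpatient and outpatient rehabilitation are pooled, but the stated ANOVA has no term for entry setting, so a likely source of variation in balance change stays in the group contrast and in the effect size meant to size the definitive trial

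*Protocol article*

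**What the plan says.** **Who enters.** Criterion 3 in the Participants section covers patients who "3) are receiving inpatient or outpatient stroke rehabilitation services". Criterion 1 asks only that they "have had a stroke (ischemic or hemorrhagic) resulting in physical impairment". Neither the ten criteria nor the exclusions set a window on time since stroke. Further therapy is allowed: "Participation in other, non-VRT exercise or rehabilitation programs post discharge does not influence their eligibility in this feasibility trial".

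**How the target is described.** The design paragraph of the Introduction speaks of "the use of VRT for ongoing stroke rehabilitation after discharge from inpatient or outpatient stroke rehabilitation". Secondary objective 2 is worded more narrowly: "after discharge from hospital-based stroke rehabilitation, compared to those who perform a program of iPad apps".

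**Recovery stage.** The Introduction puts most patients leaving inpatient stroke rehabilitation at 8–10 weeks post stroke, says most are offered outpatient therapy, and adds: "Their central nervous systems are still in a period of enhanced neuroplasticity, during which great functional change can be made".

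**Allocation.** A computer system is used to "allocate participants in a 1:1 ratio to either experimental or control groups, using permuted blocks while maintaining concealment". No stratification factor is named. The same section foresees concurrent therapy: "If the participant is undergoing rehabilitation during the study period (for example, outpatient or community-based rehabilitation".

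**Analysis.** Data management and analysis gives a mixed ANOVA with time, group and time by group. According to Outcome measures, the BBS result supplies the effect size for the definitive trial's sample size.

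**The concern.** A patient about to leave the inpatient ward and one finishing outpatient therapy are likely to be at different points of recovery. By the Introduction's own account, the first is in a phase when much change can still occur. Nothing bounds how long after stroke the second may be. The two are therefore likely to differ in expected 6-week BBS change whatever the arm.

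Comparing change removes a difference in baseline level between arms, but not a difference in rate of recovery. With 10 or 20 per arm, an uneven split of settings moves the time by group contrast. Even with a perfectly even split, the difference between settings sits in the error term. Both effects reach the BBS effect size that is to be carried forward.

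**Working it through.** **Inputs from the article.**
- Annual admissions: about 250 inpatient and 250–300 outpatient (Participants).
- 18-month pool: 375 inpatients and 375–450 outpatients (Sample size and recruitment).
- Arms: 20 per arm as planned; 10 per arm if the amended total of 20 is split 1:1 (Trial Registration).

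**Assumed.** Inpatients' mean BBS change exceeds outpatients' by d = 0.5 to 1.0 within-setting SDs in both arms. The article gives no SD and no recovery rate by setting.

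**Step 1: reproduce the pool.** 250 × 1.5 = 375; 300 × 1.5 = 450. Both agree with the article. The inpatient share is 375/825 = 45% to 375/750 = 50%, ignoring patients who pass through both programs.

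**Step 2: chance imbalance.** With N participants, K inpatients and n per arm, the number of inpatients x in one arm is hypergeometric: P(x) = C(K, x) · C(N − K, n − x) / C(N, n). The imbalance is |2x − K| / n.

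- N = 20, K = 10, n = 10, gap of 40 points or more (70%/30% or worse): x ≥ 7 or x ≤ 3. This gives 2 × (14,400 + 2,025 + 100 + 1) / 184,756 = 33,052 / 184,756 = 17.9%.
- N = 20, K = 9, n = 10, same threshold: x ≥ 7 or x ≤ 2. This gives 2 × (5,940 + 495 + 11) / 184,756 = 12,892 / 184,756 = 7.0%.
- N = 40, K = 20, n = 20, gap of 30 points or more (65%/35% or worse): x ≥ 13 or x ≤ 7, 11.3%. With K = 18 it is 11.1%. A gap of 40 points or more has about 2.5%.

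The figures at 10 per arm jump because only certain gaps are possible (0, 20, 40, … when K = 10; 10, 30, 50, … when K = 9).

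**Step 3: shift in the contrast.** Shift = imbalance × d.

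| Per arm | Gap | Shift (d = 0.5 to 1.0) | SE = √(2/n) | Shift / SE |
|---|---|---|---|---|
| 20 | 30 points | 0.15 to 0.30 SD | 0.316 SD | 0.47 to 0.95 |
| 10 | 40 points | 0.20 to 0.40 SD | 0.447 SD | 0.45 to 0.89 |

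**Step 4: error rates.** 40,000 simulated trials per scenario used half inpatients, no VRT effect, and a two-sided 5% t-test on change (equivalent to the time by group test with two time points).
- All trials together: 4.9% to 5.1%.
- Trials with a gap of 30 points or more: 6–7% (d = 0.5) and 11–13% (d = 1.0).
- Trials with no gap: about 4.2% (d = 0.5) and 2.9% (d = 1.0).

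The last line shows that balance without adjustment makes the test conservative, so stratifying alone is not enough.

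**Step 5: variance.** Pooling equal halves multiplies the variance of change by 1 + d²/4: 1.0625 at d = 0.5 and 1.25 at d = 1.0, an increase of about 6 to 25%. Required sample size is proportional to this variance, so it rises by the same 6 to 25% relative to a definitive trial that adjusts for setting.

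**The case against.** **The sample is the intended one.** A reader might infer from criterion 3 that the trial does not study patients after discharge at all. The article does not support that. The abstract, the design paragraph and the procedures all refer to discharge from either program, with the first three sessions shortly before it. Criterion 3 describes status at screening, when patients must still be in a program. The Discussion names both uses of VRT, alongside outpatient therapy and after formal rehabilitation ends. Only inpatients who go on to hospital outpatient therapy fit awkwardly under the hospital-based wording of the title and secondary objective 2, and their share is not stated. This objection stands: broad entry is defensible in a feasibility trial that reports difficulty recruiting.

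**Chance imbalance is not bias.** A reader might also infer that an uneven split invalidates the comparison. It does not: overall type I error stays near 5%, the shifts in the table are below one standard error, and the Discussion already concedes limited ability to detect differences. This stands too. It does not answer why a baseline variable that is known and plausibly prognostic should be left in the error.

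**The size rests on an assumption.** The 0.5 to 1.0 SD gap is not in the article, and 18% falls to 7% with one fewer inpatient. Both are correct, and the ranges must be shown.

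**The full protocol may say more.** Stratification factors may be named there; the article is silent rather than negative. Its analysis model, however, is written out with its factors.

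**It may be late.** Recruitment began in May 2017 and enrollment was cut in June 2018, so few may remain to be randomized. This limits stratification but not the analysis.

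**Conclusion.** The concern holds as a matter of precision and of what is carried to the definitive trial. It does not hold as a claim of bias or of a wrong population. The stated model leaves entry setting in the error of a small secondary comparison and of the BBS effect size.

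Chance imbalance of a size that matters is fairly likely: 18% (or 7%) for 40 points or more at 10 per arm, and 11% for 30 points or more at 20 per arm. The resulting shift of 0.15 to 0.4 SD and the 6 to 25% variance inflation depend on the assumed recovery gap and would shrink with it. The inflation overstates the definitive trial's sample size only if that trial adjusts for setting; for an unadjusted trial with the same mix, the pooled SD is the relevant one. That is a reason to have both. The primary feasibility objectives are not affected.

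**What to change.** 1. **Model.** In Data management and analysis, adjust the group comparison of change for entry setting. In the mixed ANOVA this means adding setting by time; a setting main effect alone would leave the time by group contrast unchanged. Alternatively, use ANCOVA on the post-intervention score with baseline and setting as covariates.
2. **Sample-size input.** Report BBS change and its SD by setting, beside the pooled figures.
3. **Allocation.** Stratify by entry setting for anyone still to be randomized. This cannot rebalance those already allocated, so it adds to item 1 and does not replace it.
4. **Wording.** State the conclusion for secondary objective 2 as covering patients discharged from inpatient or outpatient rehabilitation, with or without ongoing outpatient therapy, in line with the design paragraph of the Introduction.

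**Cost.** About one degree of freedom: the error degrees of freedom for the contrast of change go from 18 to 17 with 20 complete cases, or from 38 to 37 with 40. The ANCOVA spends one more on baseline. Entry setting is known for every participant from criterion 3, so no new data are needed. Setting is only a proxy for time since stroke and will not remove all variation in recovery stage.

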### Sample size and recruitment

No sample size calculation was performed as this is a feasibility trial. The sample size of two groups of 20 is based on available time and recruitment expectations and funding level. It is expected that having 20 participants in the VRT arm of the study will be enough to discern the feasibility of home-based VRT. It is deemed reasonable that 40 out of the estimated 375 stroke rehabilitation inpatients and the 375–450 patients who attend outpatient stroke rehabilitation over 18 months will be eligible and interested in the study. Members of the clinical care team will be made aware of the study through their clinical manager and attendance at team meetings. The study will be stopped prematurely if serious adverse effects occur.

